### *III.3.2. Number of subjects.*

Because each patient is evaluated by both navigational bronchoscopy and confocal procedure, the required number of patient can be calculated based on a non-inferiority test for paired data. (Tango T. Equivalence test and confidence interval for the difference in proportions for the paired-sample design, Statistics in medicine 17, 891-908, 1998.) . According to this test, 78 patients positive for navigational bronchoscopy are needed to show a 10 % performance difference between the techniques (alpha risk 5%, Power 80%). This proportion corresponds to a 0,74 concordance using Cohen Kappa test. Forecasted sensitivity of navigational bronchoscopy being 65%, the total number of patients required for the study is 120.

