**Experimental plan:**

Multicentric prospective controlled trial, conducted in three academic centers, specialized in interventional bronchoscopy, equipped with both navigational bronchoscopy and probe based confocal microendoscopy techniques.

Subjects with peripheral lung nodule requiring navigational bronchoscopy will be included in the study and explored using both Confocal endoscopy AND navigational bronchoscopy. Confocal probe will be inserted in the same catheter as used for the navigational bronchoscopy and confocal images will be recorded before and after fluorescein IV injection, and before sampling.

In this study, positive diagnostic criteria for the localization of peripheral nodule using confocal imaging is a solid pattern as opposed to the usual loose fibered network pattern of the normal alveolar duct. According to this criteria, the confocal imaging procedure will be considered as valid if the number of lesions localized by confocal is not inferior to 90 % of those localized by navigational bronchoscopy. Therefore, pCLE will prove valid if it can recognize at least 70 subjects out of the 78 / 120 subjects for which the navigational bronchoscopy is forecasted to localize the peripheral lesion (Cohen concordance Kappa value of 0,74 between confocal and navigational bronchoscopy).

A secondary objective will be to describe specific signs of cancer using confocal endoscopy . This will be assessed on the first 30 patients using confocal imaging obtained before and after fluorophore IV injection, in comparison to histology, and confirmed on the following 48 patients.

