#### **III.3. Patient number, statistical analysis**

##### *III.3.1. Principal criteria analysis :*

In this study, we will consider that, to be valid for the diagnosis of peripheral nodule, alveoscopy should recognize 90% or more nodules that are successfully localized and sampled using navigational bronchoscopy techniques.

Positivity criteria for alveoscopy is defined as in-vivo imaging of a solid pattern and a conclusive biopsy sampling (benign or malignant) of the lesion during one of the navigational attempt to localize the lesion. Alveoscopy will be considered negative if a normal pattern is observed, with a conclusive biopsy of the nodule in the same location.

Navigational bronchoscopy results will be considered positive in case of conclusive biopsy at the first attempt of localisation of the lesion during bronchoscopy.

Therefore, there is a possibility that final results of the study show superiority of confocal imaging over navigational bronchoscopy , if pCLE allows for a better control and correction of the position of the navigational probe during the procedure.

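### The stated alpha of 5% and power of 80% do not belong to the success rule and patient set that the protocol names: 70 or 71 of 78 is not a 5% test, and 80% power rests on an unstated true rate of 97–98%

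*Protocol*

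**What the plan says.** III.3.1 sets the criterion: "alveoscopy should recognize 90% or more nodules that are successfully localized and sampled using navigational bronchoscopy techniques".

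III.3.2 says that "the required number of patient can be calculated based on a non-inferiority test for paired data", cites Tango's method, and gives the size: "78 patients positive for navigational bronchoscopy are needed to show a 10 % performance difference between the techniques (alpha risk 5%, Power 80"%). It adds: "This proportion corresponds to a 0,74 concordance using Cohen Kappa test". It then scales up: "Forecasted sensitivity of navigational bronchoscopy being 65%, the total number of patients required for the study is 120".

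Two other places turn the criterion into a bare count. The Experimental plan in the opening summary calls pCLE valid at 70 or more of the 78. The Statistical evaluation in the Synopsis asks for 71 or more of the 78. Each ties its count to the same figure, a "Cohen concordance Kappa value of 0,74 between confocal and navigational bronchoscopy".

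The sidedness of alpha, the expected pCLE recognition rate and the expected discordance are not given.

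**The concern.** A paired non-inferiority test compares two proportions that can both vary. Once the set is restricted to patients in whom navigation succeeded, one proportion is fixed at 100% and a pCLE-only success cannot occur. Alpha and power then depend only on the pCLE rate, for which the protocol has a threshold but no expected value.

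The counts of 70 and 71 are 90% of 78 rounded down and up. They compare a point estimate with the margin and leave no room for sampling error. A team following either count as written could declare pCLE valid without any test at the stated 5% level. A team following III.3.2 would apply a much stricter rule. The primary conclusion could differ between the two on the same data.

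**Working it through.** **Inputs.** From III.3.2: 78 navigation-positives, 10% margin, alpha 5%, power 80%, 65% navigation yield, N=120, kappa 0.74. From III.3.1: the 90% criterion. From the opening summary and the Synopsis: the counts 70 and 71. Sidedness is not stated, so one-sided 5% and one-sided 2.5% are both shown. True pCLE rates are assumptions, shown as a range.

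**1. The plan's own figures.** 78/0.65 = 120, which agrees. The 78 can be reached with a one-sample formula at one-sided 2.5% and an assumed true rate of 98%:

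n = [1.960·√(0.90·0.10) + 0.842·√(0.98·0.02)]² / (0.98 − 0.90)² = 77.8, so 78.

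Other routes come close (see objection).

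**2. Reduction to one sample.** Let b be the navigation-positive, pCLE-negative patients, c the reverse, and q the restricted estimate of the probability of c. Tango's statistic is (n·0.10 − (b − c)) / √(n·(2q + 0.10 − 0.10²)). Among navigation-positives c = 0 and q = 0. At 75/78 (b = 3):

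- Tango: (7.8 − 3)/√(78·0.09) = 1.812
- One-sample score against 90%: (75/78 − 0.90)/√(0.09/78) = 1.812

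The two are the same test.

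**3. Critical count.** Exact binomial tail at a true rate of 90%, n = 78:

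| Count needed | P(count or more), true rate 90% |
|---|---|
| 70 (89.7%) | 0.622 |
| 71 (91.0%) | 0.475 |
| 74 | 0.099 |
| 75 | 0.041 |
| 76 | 0.013 |

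So 75 is needed at one-sided 5% and 76 at one-sided 2.5%. The two written counts have type I error of 62% and 48%, and 70/78 is itself below 90%.

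**4. Power of the valid test, n = 78.**

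| True recognition | 75/78 rule (5%) | 76/78 rule (2.5%) |
|---|---|---|
| 95% | 45% | 25% |
| 97% | 79% | 58% |
| 98% | 93% | 79% |

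**5. Kappa.** Take 120 patients, 78 positive on each technique and 71 shared (71/7/7/35). Observed agreement is 106/120 = 0.883, chance agreement 0.65² + 0.35² = 0.545, and kappa (0.883 − 0.545)/0.455 = 0.744. Other tables:

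- 70/8/8/34 (equal margins, 70 shared): 0.707
- 70/8/6/36 (nearly equal margins): 0.746
- 71/7/0/42 and 70/8/0/42 (no pCLE-only positives): 0.877 and 0.860
- The 78 navigation-positives alone: observed and chance agreement are both 71/78, so kappa is 0

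**6. All 120 pairs.** Kappa 0.74 with 65% in both margins implies discordance of (1 − 0.74)·2·0.65·0.35 = 11.8%. With no true difference and one-sided 5%, exact Tango power at n = 120 is 91% for a margin of 10 absolute points. The 90% criterion is a different margin on that scale: 10% of 65% is 6.5 points, and power is then 61%. Conversely, 10 points of 120 is 12 patients, or 12/78 = 15% of the navigation-positives.

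**The case against.** **The 80% is attainable.** Power among 78 navigation-positives depends on a rate that the protocol leaves open, and step 1 shows that 78 follows exactly from one choice of it. This stands. A reader might infer that the trial simply fails to deliver 80% power; the document does not support that. What it supports is that the 80% comes without the assumption that makes it true, and that the assumption is demanding.

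**The origin of 78.** It is tempting to say that 78 was a total number of pairs, relabelled as navigation-positives and divided by 0.65 a second time. With 78 total pairs and 11.8% discordance, exact Tango power is 78% at one-sided 5%, close to 80%. But the simple formula gives 73 at that discordance, the same formula with 10% discordance at one-sided 2.5% gives 78.5, and the one-sample formula gives 78. The document does not show which was used.

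**Kappa.** It does follow from 71, 78, 120 and the equal-sensitivity hypothesis, so it is not an arithmetical mistake. What stands against it is the set to which it is attached, and that the opening summary pairs it with 70, where equal margins give 0.707.

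**Which 78?** III.3.3 describes them as patients with a definite diagnosis from the procedure. III.3.1 counts navigation only at its first attempt, so on that reading pCLE-only positives could exist among them. But III.3.2 and both count rules name patients localised or sampled by navigation. The ambiguity is a further reason to name the set.

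**71/78 is a threshold, not an expected rate.** Agreed. Power of 7% at a true 91% is no defect, since any valid test against 90% has power near alpha there.

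**This can wait for an analysis plan.** The protocol itself already fixes the test, set, alpha, power and success counts, and they do not agree.

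**Conclusion.** The point holds in this form: the protocol's alpha and power do not belong to its stated success rule and analysis set. As written, 70/78 or 71/78 would pass an exactly-90% technique 62% or 48% of the time. A valid test in the same 78 needs 75 (one-sided 5%) or 76 (one-sided 2.5%), and has about 80% power only at a true recognition of about 97% or 98%.

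The type I error figures rest only on n = 78 and independent patients. The power figures rest also on the assumed true rate. The figures for all 120 pairs rest on kappa 0.74, a 65% yield on both techniques and no true difference; treating 90% of navigation as a fixed 6.5 points is an approximation.

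This needs correction before the primary result is read, because the written counts alone could declare validity. Neither an underpowered trial nor a double division by 0.65 is established.

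**What to change.** Rewrite III.3.2 and align the opening summary and the Synopsis, keeping N=120:

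1. Name one analysis set, the sidedness and the margin scale.
2. Make the primary test the exact one-sample test of pCLE recognition against 90% among navigation-positives. Replace both the 70 and the 71 rule with its critical count: 75/78 at one-sided 5% or 76/78 at one-sided 2.5%, recalculated for the number of navigation-positives actually obtained. With 120 patients and a 65% yield, 78 or more are reached with probability of only 54%.
3. State power with its assumption: about 80% if true recognition is 97% (one-sided 5%) or 98% (one-sided 2.5%), and 45% or 25% at 95%.
4. Remove the kappa statement in all three places, or label it as the 120-patient table under equal sensitivity.

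A Tango test on all 120 pairs is an alternative only if a pCLE result is defined for navigation-negative patients. II.1.1 starts pCLE after a successful localisation, and III.3.1 requires a conclusive biopsy for either pCLE result, so some patients have none. If chosen, the margin must be stated in absolute points, with power of about 91% (10 points) or 61% (6.5 points) at one-sided 5%.

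The cost is one rewritten paragraph and two aligned sentences, with no extra patients. The price is a stricter success count and a less comfortable power statement.

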### *III.3.3. Secondary criteria analysis :*

Positive predictive value of confocal imaging for the differentiation of benign versus malignant lesion will be calculated based on histology of the lesion and pertinent in vivo imaging items that will be describe during the study. This semiology will be described from the first 30 patients (including 20 malignant lesions) among the 78 patients for which a definite diagnosis is obtained by the procedure.

The value of this semiology will be confirmed on the 48 further patients.

### **IV.2 Duration of the study, feasibility .**

120 patients presenting with a peripheral pulmonary nodule requiring navigational bronchoscopy will be included in the three centers. Patient recruitment will be competitive, during a 30 months period, with a forecasted inclusion rate of one to two patients per center each month. The total duration of the study will be 3 years including 6 month follow up. The choice of the reference navigational technique will be determined by the investigator for each patient before the procedure.

Feasibility of the project relies on :

- The large experience of Pr [name] in the confocal technique
- The recognized experience of each investigator in interventional bronchoscopy and navigational bronchoscopy (both EBUS and EMN) with at least 50 procedures already performed in each center, and the fact that the centers are currently equipped with Cell vizio.
- Strong professional links between investigators already exist, as the three investigators have participated to multicentric trials coordinated by Pr [name], such as Seleprebb study (Clinical trial identifier NCT00213603, supported by PHRC 2002) and EVIEPEB study (Clinical trial identifier NCT00960271, supported by INCa 2007). The three investigators are active members of the GELF group (groupe d'endoscopy de langue Française), coordinated by Pr [name].

### **IV.3. Inclusions**

Patients will be prospectively included in each center, according to the French regulations for clinical trials, and after AFSSAPPS authorization and Ethical comity approval of the study. Quality assurance will be provided by the Rouen University Hospital, unique sponsor of the study. Informed consent will be acquired from the patient before the procedure according to Helsinki rules.

Each patient inclusion will be declared in real time to the Rouen University direction of research and innovation by Fax

#### *IV.3.1. Inclusion criteria*

- Patients with a peripheral lung nodule accessible by navigational bronchoscopy and cell vizio according to Investigator evaluation of the CT scan.
- 18 years old or more.
- Affiliation to french social security insurance.
- Signed informed consent for the procedure.

#### *IV.3.2. Non-Inclusion criteria*

- Apical and dorsal segment lesions of both upper lobes, which are currently not accessible using cell vizio Alveoflex miniprobos.
- Severe respiratory insufficiency that will not allow the bronchoscopy procedure
- Uncorrected bleeding disorders
- History of pneumonectomy or exploration contralateral to a non functional lung,
- Pregnant or breast feeding woman, or person not authorized to participate to a clinical trial according to L1121-6 et L1121-8 of French Code de la santé Publique, concurrent participation to another clinical trial

### **IV. 4. Endoscopy procedure**

- Alveoscopy procedure will be performed according to the procedure validated at the Rouen University Hospital, in gently advancing the confocal miniprobe through the bronchoscope working channel and distal bronchus until the alveolar fluorescent signal could be obtained. The probe will then stay in place

5 to 30 seconds for alveolar sequence recording

- Navigational bronchoscopy (EBUS / EMN) will be performed according to the usual validated procedure.
- Confocal imaging of the peripheral nodule will be performed by entering the confocal miniprobe into the extended working channel during the navigational bronchoscopy procedure as described in chapter II.1.1..
- Confocal exploration duration will not exceed 10 minutes for the totality of the endoscopy procedure.
- Usual monitoring (EKG, transcutaneous arterial saturation) will be recorded continuously during the procedure, and chest radiograph performed after the bronchoscopy to control the absence of pneumothorax.
- Patient could be discharged after the procedure after one hour, and physical examination.

#### **IV. 5. Tolerance. Interruption of the study.**

Tolerance data will be collected and analyzed prospectively. Interruption of the study could be decided by the sponsor of the study if justified based on this safety data surveillance.

#### **IV.6. Role of each team**

The study will be conducted in three academic centers.

1. CHU de Rouen
2. CHU de Toulouse
3. CHU de Saint-Etienne

Each Investigator will be responsible for the local recruitment into the study and will conduct the study in his center according to good practice guidelines. All investigators will participate to the central review of the patients' charts

Confocal image analysis for initial description of malignant lesions semiology (secondary objective) will be performed prospectively for the 38 first informative cases. These data will be analyzed jointly by the three principal investigators in order to describe confocal semiology that could differentiate malignant from benign lesions.

After this step, this confocal semiology will be recorded on the following patients, and data analyzed by an independent observer, blindly from the results of the histology.

#### **IV.7. Duration of the study**

Start of the study : september 2011

Inclusion : 30 months

Chart's review and validation : 6 months after the endoscopic procedure

Total duration of the study : 3 years.

**V-Ancillary study (submitted to the ethical committee and approved July 20th, 2012 N° approval CPP 2011/30 Amdt 1) .**

**At the Rouen University Hospital, and Toulouse University Hospital, an ancillary study will be performed in a subset of the study population, using a 0.6 mm modified Cholangioflex® miniprobe in order to explore the nodules in the upper lobe segments. The objectives of the ancillary study are to confirm the possibility to reach the upper lobe, and to compare the imaging performances of this probe to the standard 1 mm Alveoflex® probe.**
